### Study design

This prospective multicentric (Clinique Victor Hugo-Centre Jean Bernard, Le Mans, France and Centre Hospitalier du Mans, Le Mans, France) study will consist of an 18 month follow-up of a women cohort with breast cancer. Four visits will be scheduled (the study timeline is presented in Fig. 1). Detailed patient assessments will be performed before treatment begins (visit 1: diagnosis); during the week after completion of the first-line treatment, or 6 months after diagnosis, whichever comes first (visit 2); and then 12 and 18 months after diagnosis (visit 3 and 4, respectively). This study has been approved by the French ethics committee of human research CPP SUD EST VI (IDRCB: 2019-A02525–52) and will be performed according to the Declaration of Helsinki. Furthermore, this study protocol has been written in accordance with the SPIRIT guidelines (SPIRIT Checklist provided in Additional file 1) and is registered in a database (ClinicalTrials.gov, NCT04391543, May 2020). In order to longitudinally assess the evolution of biopsychosocial dimensions of CRF, the same procedure will be followed for each visit. Each session will last 1.5 h and will be composed of anthropometric data collection, a semi-structured interview, cognitive tests, postural control tests, neuromuscular fatigability tests and a cardiorespiratory fitness test. Clinical and biological data will be collected during medical follow-ups. In addition, participants will be asked to wear an actigraphy device (received by mail one week prior to each experimental session) and to complete questionnaires to assess psychological aspects and quality of life.

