### Clinical and biological data

As experimental sessions will accompany medical follow-ups, clinical and biological data will be also recorded. Cancer stage and details related to treatments (e.g., type, duration and dose) will be recorded in a medical file by their oncologist. Venous blood samples will be collected by medical staff. Plasma will be obtained after a 10 min centrifugation at 4 °C, then divided into aliquots and stored at − 80 °C until analysis. Following assays will be performed on plasma for the assessment of inflammation (IL-6, TNFɑ, IL-8, IL-1β). Abdominal computed tomography (CT) images at the L3 level will be taken by medical staff on two occasions (Visit 1 and Visit 2). The surface of the muscular tissues will be selected according to the CT Hounsfield unit and normalized to stature in order to calculate the lumbar skeletal muscle index (LSMI). A cut-off value (LSMI < 38.5cm^2^/m^2^) will be used to characterize sarcopenia [49]. Cancer stage and treatment; sarcopenia; and IL-6, IL-1β, TNFɑ (pg/mL) concentrations will be considered in the SEM.

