### Sample size

A sample size of *n* = 200 patients has been chosen on the basis of resource constraints [53]. 200 correspond to a 15% inclusion rate of the patients meeting the inclusion criterion during a 24 months inclusion period and including a 20% potential drop-out rate. Considering this sample size, a sensitivity power analysis performed with G-power (*F* tests family, linear multiple regression, *R*^*2*^ increase) to estimate the smallest effect size we could detect with 90% power regarding our main independent variable (i.e., CRF) at the level of analysis with the lowest power (i.e., level 2, between-person level). This analysis, with a power of 0.90, an α level of 0.05 and 6 predictors (i.e., 6 latent variables), revealed that the smallest effect size we could detect with 90% power, at this level of analysis, is *f*^*2*^ = 0.09, which correspond to a small to medium effect.

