### Statistical analysis

Hypotheses will be addressed by constructing a biopsychosocial model of the relationships among biological, physical, emotional, cognitive and social dimensions of CRF using multilevel SEM. SEM is particularly well-suited to this type of analysis because it simultaneously accounts for multiple interactive relationships among variables, easily handles multiple sources of variance, and permits testing of hypothesized directional relationships [54, 55]. Consequently, the results of SEM analyses facilitate inferences regarding the relationships among variables [56]. Relations between the manifest variables and their underlying latent constructs in a hypothesized biopsychosocial model predicting CRF are presented in Table 3. The model will be tested with the maximum likelihood method using Lavaan *R* package for SEM [57]. A primary cross-sectional analysis will be completed using data collected at each visit, and then subsequently by using the longitudinal data set. The models’ fit was assessed by examining the minimum discrepancy (CMIN/DF), the probability level (*p*-value), the Bentler-Bonett normed fit index (NFI), the comparative fit index (CFI), the Tucker–Lewis-Index (TLI), and the root-mean-square error of approx- imation (RMSEA). A satisfactory model fit is indicated by a CMIN/DF ratio below 2.00 [58], a *p*-value over 0.05 [59], a NFI over 0.95 [60], a TLI over 0.90 [61], a CFI over 0.93 [62], and a RMSEA below 0.05 [63]. All non-significant paths were deleted according to the methods described by MacCallum [64].

**Table 3 Tab3:** Latent and manifest variables included in the model built by SEM

Latent variable	Manifest variable	Test
**Social function**	Family sociability	Semi-structured interview
	Friendly sociability	Semi-structured interview
	Professional sociability	Semi-structured interview
	Income	Semi-structured interview
**Cognitive function**	MoCA total score	MoCA
	TMT time	TMT
	Interference score	Stroop
**Physical function**	95% confidence ellipse area	Postural test
	F_A_	Neuromuscular fatigability test
	VA	Neuromuscular fatigability test
	Db100	Neuromuscular fatigability test
	Power output at LT1	Cardiorespiratory fitness test
	Sleep efficiency	Actigraphy
	Total activity duration	Actigraphy
	Sarcopenia	Abdominal CT at the L3 level
**Biological function**	Cancer stage	Medical file
	Cancer treatment	Medical file
	IL-6 concentration	Blood sample
	IL-1β concentration	Blood sample
	TNFɑ concentration	Blood sample

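### Table 3 makes cancer stage and treatment indicators of the same latent Biological function as three cytokines: the block cannot be fitted as listed at visit 1 or within person, and elsewhere its meaning depends on loadings and coding

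*Protocol article*

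**What the plan says.** - **Variables.** Clinical and biological data puts "Cancer stage and treatment; sarcopenia; and IL-6", IL-1β and TNFα into the SEM. Table 3 places sarcopenia under Physical function. It makes cancer stage, cancer treatment, IL-6, IL-1β and TNFα the five manifest variables of Biological function.
- **Direction.** Statistical analysis describes the latent constructs as underlying the manifest variables, which is the language of a reflective model. Neither stage nor treatment is given a separate covariate role.
- **Estimation.** "The model will be tested with the maximum likelihood method" in lavaan, first cross-sectionally at each visit and then on the longitudinal data, within a multilevel SEM. Non-significant paths are deleted.
- **Timing.** Visit 1 takes place "before treatment begins (visit 1: diagnosis". Stage (I to IIIc) is an entry criterion in Table 2. Treatment type, duration and dose are recorded, but the coding of the single treatment variable is not given.
- **Rationale.** The Background treats stage and treatment type as clinical data, apart from the biological parameters measured in blood. The biological column of Table 1 covers inflammation, metabolism, hormones and immunity, and contains neither stage nor treatment.

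**The concern.** A reflective factor states that one latent state produces all its indicators and explains the correlations among them. That is not credible for stage and treatment beside plasma cytokines. Stage describes the tumour at diagnosis, and treatment is a decision that follows from it. Table 3 thus merges what the Background keeps apart.

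Two things are at stake. First, an indicator that cannot vary cannot be fitted, and this affects stage at the within-person level and treatment received at visit 1. Second, if stage and treatment correlate with each other more than with the cytokines, a single factor has to favour one cluster. The path from Biological function to CRF then means either inflammation or disease and treatment severity, and the label does not say which. Because non-significant paths are dropped, a path that is small only because the factor settled on the wrong cluster could remove biology from the final model.

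**Working it through.** **1. The plan's own figure.** The sample "patients has been chosen on the basis of resource constraints", and the sensitivity analysis is run "with a power of 0.90, an α level of 0.05 and 6 predictors (i.e., 6 latent variables" and "at the level of analysis with the lowest power (i.e., level 2, between-person level". For a noncentral F test with u = 6, v = 200 − 6 − 1 = 193 and λ = 200f², power at f² = 0.09 (λ = 18) is 0.9001. The stated 0.09 reproduces. It does not depend on how indicators are assigned to factors, so it neither supports nor is harmed by this point.

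**2. Can the block be fitted as listed?**
- Visit 1, treatment meaning treatment received: its variance is 0, and the 5 × 5 indicator covariance matrix has rank 4.
- Within person, stage recorded once: its within-person variance is 0, and the within-level matrix again has rank 4 of 5.
- Maximum likelihood needs a nonsingular matrix, so the five-indicator block fails in both places.
- The three cytokines alone have rank 3 of 3 and identify one factor (three loadings, just identified). In a simulation with a true inflammation–CRF correlation of 0.310, the cytokine-only factor returned 0.310.

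**3. Where it can be fitted, what does the factor represent?** All inputs here are assumptions, because the article gives no loadings. There are two stage/treatment indicators with loading a on severity, three cytokines with loading c on inflammation, and four CRF indicators with loading 0.8. The severity–inflammation correlation is 0.1, the true inflammation path 0.30 and the severity path 0. The implied severity–CRF correlation is 0.1 × 0.30 = 0.03.

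The Table 3 structure (one factor for the five biological indicators, one for CRF) was fitted to the implied correlation matrix by minimising F = ln|Σ| + tr(SΣ⁻¹) − ln|S| − p, with p = 9. There are 9 × 10/2 = 45 moments and 9 + 9 + 1 = 19 parameters, so df = 26. Path in the best-fitting solution:

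| a \ c | 0.4 | 0.5 | 0.6 | 0.65 | 0.7 |
|---|---|---|---|---|---|
| 0.4 | 0.30 | 0.30 | 0.30 | 0.30 | 0.30 |
| 0.5 | 0.30 | 0.30 | 0.30 | 0.30 | 0.30 |
| 0.6 | 0.050 | 0.30 | 0.30 | 0.30 | 0.30 |
| 0.7 | 0.039 | 0.047 | 0.30 | 0.30 | 0.30 |
| 0.8 | 0.035 | 0.038 | 0.042 | 0.30 | 0.30 |

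The best solution is a cytokine factor in 19 of 25 cells and a stage/treatment factor in 6.

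A hand check shows why. A cytokine factor leaves the stage–treatment correlation a² unexplained, at a cost of about −ln(1 − a⁴). A stage/treatment factor leaves three cytokine correlations c² unexplained, at a cost of at least about −ln[(1 − c²)²(1 + 2c²)].
- a = 0.7, c = 0.5: −ln(1 − 0.2401) = 0.275 against −ln(0.75² × 1.5) = 0.170. Stage/treatment wins.
- a = 0.7, c = 0.6: 0.275 against −ln(0.64² × 1.72) = 0.350. Cytokines win.

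At a = 0.8, c = 0.65 the two solutions nearly tie: F = 0.5200 (path 0.300) against 0.5324 (path 0.045). With 160 completers (200 × 0.80, one reading of "including a 20% potential drop-out rate"), the gap is 160 × 0.0124 = 2.0 chi-square points, and RMSEA is √(0.52/26) = 0.141. Moving c to 0.60 or 0.70 makes the gap about 20 points one way or 31 the other.

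**4. Treatment coding.** A separate simulation assumed three stage groups, three treatment groups, treatment dependent on stage, chemotherapy affecting CRF, and a true inflammation–CRF correlation of 0.31.
- Cytokine loadings 0.6 to 0.7: the path was 0.310 to 0.312 under all four codings tried. Stage and treatment loaded about 0, so their effect disappears from the model. The misfit component of chi-square at n = 200 ran from 2.8 to 52.6 (df 26) with coding alone.
- Cytokine loadings 0.4 or 0.5: coded any chemotherapy yes/no, the factor became stage/treatment (loadings 0.46 and 1.00, cytokines 0) with path 0.17. Coded any radiotherapy yes/no, it stayed a cytokine factor with path 0.31.

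**The case against.** **The biological path itself is estimable.** A reader might infer from step 2 that the path to CRF cannot be estimated at visit 1 or within person. That is not so: three time-varying cytokines identify a factor in both places. Only the block as listed fails.

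**The degeneracy depends on readings that the article leaves open.** Stage could be declared a between-person variable, and planned rather than received treatment would vary at visit 1. This is fair, and coding and level are often left to the analysis plan. But either choice changes only where the model runs. Stage and treatment would still be indicators of a state shared with cytokines, and the article does fix that assignment.

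**The switch in meaning is conditional.** A reader might conclude that the path is arbitrary in general, or that sampling noise decides which answer is reported. The grid does not support that. Most cells return 0.30, and the near-tie occurs in one cell only.

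**The plan's fit limits would object.** It asks for RMSEA below 0.05, and the near-tie example has 0.141. With a = 0.5, however, RMSEA is about 0.05. These values belong to a nine-variable extract, and the full model's indices would differ. A failed fit index also does not show which block is wrong or what its path means.

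**The reflective direction is inferred.** It rests on Table 3 and the wording about underlying constructs, and no path diagram is shown. This stands as a caveat, but the article states no other role for stage and treatment.

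**Some nearby criticisms do not hold as errors.** IL-8 is covered by "Following assays will be performed on plasma for the assessment of inflammation" and then left out of the SEM in both the text and Table 3, which is a consistent selection. The documents give nothing on cytokine skewness, and naming maximum likelihood does not exclude robust corrections.

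**Conclusion.** The point holds in limited form: the measurement model for Biological function is misspecified as written. With stage recorded once and treatment meaning treatment received, the five-indicator block is singular within person and at visit 1 (rank 4 of 5 in each). Elsewhere, an assumed true path of 0.30 is returned as about 0.30 in most settings, but as about 0.04 to 0.05 when cytokine loadings are low relative to stage/treatment loadings (0.5 against 0.7, or 0.6 against 0.8). When the cytokines win, the effect of stage and treatment is lost. These sizes rest on assumed loadings and correlations. They show the mechanism and do not predict this study's result. The documents do not support calling the biological path inestimable or arbitrary in general. Since the assignment settles what one of the five explanatory paths means, it should be corrected before any model is fitted.

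**What to change.** Remove cancer stage and cancer treatment from Biological function in Table 3, and define that factor by IL-6, IL-1β and TNFα. Enter stage and treatment as observed, dummy-coded covariates: stage at the person level, treatment received from visit 2 on. Give both paths to CRF and to the latent functions, and state the treatment coding. Amend the matching sentence in Clinical and biological data.

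The cost is a few more regression parameters and a change of specification text. No new data are needed. Adding the already assayed IL-8, log-transforming the cytokines and using a robust estimator are optional.

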### Participant-reported outcomes

One week prior to each experimental session, participants will receive by post self-assessment questionnaires about quality of life (EORTC QLQ-C30), CRF (EORTC QLQ-FA12), coping strategies (Brief Cope) and anxiety-depression symptoms (The Hospital Anxiety and Depression Scale - HADS). Participants will be asked to complete questionnaires, alone in quiet conditions, and bring it back the day of the experimental session. The subsequent instructions will be provided: “Please answer all questions yourself by circling the number that best applies to you. The information provided will remain strictly confidential. Take as much time as necessary. There are no “right” or “wrong” answers.”

The EORTC QLQ-C30 Fatigue scale score (FA item) will be used to assess the general degree of CRF (ranging from 0 to 100; with higher levels indicating a greater degree of CRF), with a threshold for clinical importance of 39 [50]. EORTC QLQ-FA12 subscales will be used to assess physical, cognitive and emotional dimensions of CRF [51]. The HADS subscale scores (/21) will be used to assess anxiety and depression, respectively [52]. In the SEM, general degree of CRF (%); dimensions of CRF (%) (physical, cognitive and emotional); coping scores (/8); and anxiety and depression scales (/21) will be considered.

### Actigraphy

One week prior to each experimental session, participants will be asked to wear a portable device (eTact®, BodyCap, Caen, France) containing a tri-axial accelerometers enabling to record every acceleration from the body (sampling frequency: 25 Hz, measurement range: 0.1-2G, sample measurement: 1 min). They will be advised to wear the device continuously for 7 days (days and nights) regardless of daily activities. Sleep characteristics will be obtained using the eTact® Analysis software (BodyCap, Caen, France), which assess the individual sleep quality based on the actigraphy data collected over selected periods. Considered sleep parameter will be sleep time (i.e, duration of effective sleep period) and sleep efficiency (i.e., percentage of time spent sleeping during the rest period). From the software, total activity duration during wake period will be calculated as the accumulated time in each activity intensity band (i.e., low, moderate and intense). In addition, participants will be asked to complete a sleep diary (including estimated sleep onset and offset hour) during the actigraphy measurements. Total activity duration (min) and sleep efficiency (%) will be considered in the SEM.

### Sample size

A sample size of *n* = 200 patients has been chosen on the basis of resource constraints [53]. 200 correspond to a 15% inclusion rate of the patients meeting the inclusion criterion during a 24 months inclusion period and including a 20% potential drop-out rate. Considering this sample size, a sensitivity power analysis performed with G-power (*F* tests family, linear multiple regression, *R*^*2*^ increase) to estimate the smallest effect size we could detect with 90% power regarding our main independent variable (i.e., CRF) at the level of analysis with the lowest power (i.e., level 2, between-person level). This analysis, with a power of 0.90, an α level of 0.05 and 6 predictors (i.e., 6 latent variables), revealed that the smallest effect size we could detect with 90% power, at this level of analysis, is *f*^*2*^ = 0.09, which correspond to a small to medium effect.

### Statistical analysis

Hypotheses will be addressed by constructing a biopsychosocial model of the relationships among biological, physical, emotional, cognitive and social dimensions of CRF using multilevel SEM. SEM is particularly well-suited to this type of analysis because it simultaneously accounts for multiple interactive relationships among variables, easily handles multiple sources of variance, and permits testing of hypothesized directional relationships [54, 55]. Consequently, the results of SEM analyses facilitate inferences regarding the relationships among variables [56]. Relations between the manifest variables and their underlying latent constructs in a hypothesized biopsychosocial model predicting CRF are presented in Table 3. The model will be tested with the maximum likelihood method using Lavaan *R* package for SEM [57]. A primary cross-sectional analysis will be completed using data collected at each visit, and then subsequently by using the longitudinal data set. The models’ fit was assessed by examining the minimum discrepancy (CMIN/DF), the probability level (*p*-value), the Bentler-Bonett normed fit index (NFI), the comparative fit index (CFI), the Tucker–Lewis-Index (TLI), and the root-mean-square error of approx- imation (RMSEA). A satisfactory model fit is indicated by a CMIN/DF ratio below 2.00 [58], a *p*-value over 0.05 [59], a NFI over 0.95 [60], a TLI over 0.90 [61], a CFI over 0.93 [62], and a RMSEA below 0.05 [63]. All non-significant paths were deleted according to the methods described by MacCallum [64].

**Table 3 Tab3:** Latent and manifest variables included in the model built by SEM

Latent variable	Manifest variable	Test
**Social function**	Family sociability	Semi-structured interview
	Friendly sociability	Semi-structured interview
	Professional sociability	Semi-structured interview
	Income	Semi-structured interview
**Cognitive function**	MoCA total score	MoCA
	TMT time	TMT
	Interference score	Stroop
**Physical function**	95% confidence ellipse area	Postural test
	F_A_	Neuromuscular fatigability test
	VA	Neuromuscular fatigability test
	Db100	Neuromuscular fatigability test
	Power output at LT1	Cardiorespiratory fitness test
	Sleep efficiency	Actigraphy
	Total activity duration	Actigraphy
	Sarcopenia	Abdominal CT at the L3 level
**Biological function**	Cancer stage	Medical file
	Cancer treatment	Medical file
	IL-6 concentration	Blood sample
	IL-1β concentration	Blood sample
	TNFɑ concentration	Blood sample
**CRF**	FA item score	EORTC QLQ-C30
	Physical subscale	EORTC QLQ-FA12
	Cognitive subscale	EORTC QLQ-FA12
	Emotional subscale	EORTC QLQ-FA12
**Emotional function**	Coping score	Brief Cope
	Anxiety scale	HADS
	Depression scale	HADS
	Maximal COP velocity	Postural test

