## Methods/design

### Study population

Two hundred women newly diagnosed with breast cancer by an oncologist and satisfying inclusion and exclusion criteria (Table 2) will be informed of the study protocol. If interested, patients will receive an information letter from their oncologist and will be given the opportunity to ask any questions pertaining to it. After a 48 h period of reflection, study coordinators will phone the patients to confirm their participation, obtain a written consent form and schedule their first visit.

**Table 2 Tab2:** Inclusion and exclusion criteria

Inclusion criteria	• Patients care by chemotherapy or radiotherapy in Clinique Victor Hugo-Centre Jean Bernard, Le Mans, France or in Centre Hospitalier du Mans, Le Mans, France
	• Patients with breast cancer diagnosis (Stage I to IIIc)
	• Aged ≥18 and ≤ 80 years
	• Approval received from oncologist
	• ECOG Performance Status ≤2
	• French speaking (able to understand questionnaires and instructions related to study procedures)
	• Written informed consent obtained
**Exclusion criteria**	• Comorbidities related to fatigue symptoms
	• Polyneuropathy, amyotrophy or myasthenic syndrome diagnosis
	• Contraindications to physical activity or to experimental procedures
	• Antidepressants, psychostimulants, psychotropics, antiépileptics or benzodiazepine based treatment
	• Previous or current psychosis, bipolarity or severe depression symptoms
	• History of chronic fatigue, stroke or musculoskeletal disorders
	• Participant is pregnant

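### The NFI cut-off of 0.95 is out of reach for the per-visit models at 160-200 women, even when the model is exactly right, unless nearly all indicators load above about 0.9

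*Protocol article*

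**What the plan says.** In the protocol article, the Statistical analysis section plans maximum likelihood SEM in lavaan, first cross-sectionally on each visit's data and then on the longitudinal data set. On fit it says "A satisfactory model fit is indicated by a CMIN/DF ratio below 2.00", adds a p-value above 0.05, and continues with "a NFI over 0.95 [60], a TLI over 0.90 [61], a CFI over 0.93 [62], and a RMSEA below 0.05 [63". The six cut-offs are joined by 'and'. No index is ranked above another, there is no 'most of these' rule, and no small-sample adjustment is stated.

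Table 3 lists 28 manifest variables on 6 latent variables: social 4, cognitive 3, physical 8, biological 5, CRF 4, emotional 4.

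The Sample size section says that 200 "has been chosen on the basis of resource constraints", "including a 20% potential drop-out rate". A per-visit model therefore has between about 160 (200 × 0.8) and 200 women. The only quantitative support is a regression sensitivity analysis.

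**The concern.** NFI compares the model chi-square with that of the null model and makes no allowance for degrees of freedom. In a sample that is small relative to the number of indicators, even a correct model has a chi-square near its degrees of freedom. That amount stays in the ratio as a shortfall unless the null-model chi-square is very large. A fixed cut-off of 0.95 can then be missed because of sample size and indicator count alone.

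The biopsychosocial model is the purpose of the study. If the stated definition of satisfactory fit fails a correct model as surely as a wrong one, then for the per-visit models the NFI result says nothing about the theory and is practically known before any data exist.

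**Working it through.** **The plan's own figure.** The sensitivity analysis is run "with a power of 0.90, an α level of 0.05 and 6 predictors (i.e., 6 latent variables" and gives f² = "0.09, which correspond to a small to medium effect". With N = 200, the noncentral F has 6 and 193 df and noncentrality 0.09 × 200 = 18. Power is 0.900, so the figure reproduces. It concerns an R² increase in a regression and says nothing about whether SEM fit cut-offs can be met.

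**Inputs.** From the article: 28 indicators, 6 latents, 160-200 women per visit, ML, six cut-offs. Assumed, because the article does not give them: each indicator loads on one latent, no residual covariances, normal data, uniform standardised loadings of 0.5-0.95, and equal latent correlations of 0.2-0.6.

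**Degrees of freedom.**
- Moments: 28 × 29 / 2 = 406.
- Free parameters: 28 loadings + 28 residual variances + 15 latent covariances = 71. Regressing CRF on the other five latents gives the same count, 10 covariances + 5 paths.
- Model df: 406 − 71 = 335. Null-model df: 28 × 27 / 2 = 378.

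**What the cut-off demands.** NFI = 1 − χ²(model)/χ²(null). NFI > 0.95 requires χ²(null) > 20 × χ²(model). With χ²(model) = 335 that is 6,700. The null chi-square is about 378 + N × (−ln|R|), where R is the correlation matrix that the model implies. So −ln|R| must be at least (6,700 − 378)/200 = 31.6 with 200 women, or (6,700 − 378)/160 = 39.5 with 160.

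**What a correct model delivers.** Expected NFI ≈ 1 − 335/(378 + N × (−ln|R|)). For loadings of 0.7 and latent correlation 0.4, −ln|R| = 9.83. With N = 200 this gives 1 − 335/(378 + 1,966) = 0.857. The same formula, beside mean NFI from simulation, at latent correlation 0.4:

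| Loading | N=160 formula | N=160 simulated | N=200 formula | N=200 simulated |
|---|---|---|---|---|
| 0.5 | 0.62 | 0.60 | 0.67 | 0.65 |
| 0.6 | 0.74 | 0.72 | 0.78 | 0.77 |
| 0.7 | 0.83 | 0.82 | 0.86 | 0.85 |
| 0.8 | 0.89 | 0.88 | 0.91 | 0.90 |
| 0.9 | 0.935 | 0.93 | 0.947 | 0.94 |

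The simulated values are slightly lower because the mean chi-square of a correct model at this N is above 335 (352-367). Over loadings of 0.5-0.85 and correlations of 0.2-0.6, the formula spans about 0.59-0.92 (N = 160) and 0.64-0.93 (N = 200).

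**Share of samples in which a correct model meets all six cut-offs** (200 to 1,000 simulated samples per setting):

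| Loading | N=160 | N=200 |
|---|---|---|
| 0.5-0.85 | 0% | 0% |
| 0.90 | about 0% | 6-24% |
| 0.92 | 0-3% | 45-70% |
| 0.95 | 57-71% | 78-80% |

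A mixed pattern with loadings of 0.3-0.85 gives expected NFI of about 0.78 and 0.81. Expected NFI reaches 0.95 only at uniform loadings of about 0.91 (N = 200) or 0.94 (N = 160).

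**Which criterion causes the failure.** With NFI removed and the other five kept, a correct model passes in about 64-75% of samples at N = 160 and 76-81% at N = 200 (loadings 0.5-0.9, correlation 0.4). At loadings of 0.7 every sample met CFI, TLI and RMSEA. The main remaining loss is the p-value criterion, which rejects a correct model in about 18-30% of samples.

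**Redundancy.** The 5% critical value on 335 df is 378.7. Hence p > 0.05 already implies CMIN/DF < 378.7/335 = 1.13, and RMSEA below √[(378.7 − 335)/(335 × N)], about 0.029 (N = 160) or 0.026 (N = 200).

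**The case against.** **The cut-offs may be guidance.** The article speaks of examining indices and of what indicates satisfactory fit. It does not say that one miss rejects the model, and it attaches no decision to a miss. A reader might infer a strict accept-or-reject rule that would reject the biopsychosocial model in every analysis. The text does not go that far. It does define satisfactory fit by six conditions joined by 'and', and that definition is what a correct per-visit model cannot meet.

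**The longitudinal model has more data.** This stands. Four visits of 160-200 women give 640-800 records. Treating 800 records as independent, which is optimistic, a correct model still passes 0% of the time at loadings of 0.5-0.6 but about 90% at 0.7 or more. The multilevel model itself was not simulated.

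**The 335 df is not in Table 3.** This also stands. Table 3 lists variables, and the parameter count is an assumption. The model also changes by visit, because CT is taken only at Visits 1 and 2. Without sarcopenia there are 27 indicators and, by the same count, 378 − 69 = 309 df. Expected NFI at N = 160 and loadings of 0.7 is still 0.83. Cutting to three indicators per latent (18 indicators, 120 df) gives about 0.80-0.93 at loadings of 0.6-0.8. The direction does not depend on the exact count.

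**Respecification.** A reader might infer that the cut-off will drive data-led model changes. The article does not support this: it plans to delete non-significant paths without linking that to fit.

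**Conclusion.** The point holds for the per-visit cross-sectional models. At 160-200 women, NFI above 0.95 is essentially unattainable for an exactly correct model at uniform loadings up to about 0.85, so the six cut-offs together are met in about 0% of samples. Passing becomes likely only if nearly all 28 indicators load above about 0.9. That is implausible for latents that combine cancer stage with cytokines, sleep efficiency with evoked force, or HADS scores with centre-of-pressure velocity.

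It would be tempting to name the chi-square criterion as an equal cause. It is not: it adds a false rejection of about 18-30% where 5% is intended, while NFI alone produces the near-certain failure. The redundancy of CMIN/DF is harmless.

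The result rests on assumed loadings, latent correlations, simple structure and normal data. It should be fixed, but it does not undermine the study: CFI, TLI and RMSEA are already stated and carry usable fit information.

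**What to change.** In the Statistical analysis section, remove NFI from the criteria for satisfactory fit, or state that it is reported descriptively only. Judge fit on the CFI, TLI and RMSEA cut-offs already given. Compute the chi-square p-value with a small-sample (Swain or Bartlett-type) correction. CMIN/DF need not be deleted. Abandoning the chi-square criterion altogether is a debatable choice that this point does not require.

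The cost is wording only, with no change to data collection or sample size. The downside is one fewer nominal criterion.
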